#### Criteria for discontinuing or modifying allocated interventions {11b}

In this study, following withdrawal criteria apply:Patients request without giving reasonsAdministrative decision by the investigatorPregnancySignificant protocol deviationSubject noncomplianceAdverse eventOther safety concern of the investigator or sponsorLost to follow-up

The sponsor is authorized to discontinue the study due to relevant medical/administrative causes. The reasons for the discontinuation of the study have to be documented in detail. Patients, who are still under treatment at the time of discontinuation, have to be examined for a final investigation, which will be documented in the CRF. If the investigator has any ethical qualms concerning the continuation of the study, this has to be immediately reported to the sponsor.

The sponsor is authorized to discontinue the study, if.The recruitment rate of patients is not sufficientSerious, non-resolvable problems of quality of the collected data evolveUnpredictable circumstances in the particular study centers appear, which do not allow a continuation of the studyNew scientific findings during the study’s run-time do not allow a continuation of the study

The study administration is able to decide about the discontinuation of the study in agreement with the sponsor, the Data Safety Monitoring Board, or the protocol committee.

The study must be closed on completion. As far as possible, premature closure should occur after mutual consultation. Depending on local legislation, it may be necessary to inform the ethics committees and the regulatory authorities when the study site is closed.

Upon closure of the entire study or a single center, all study materials (completed, partially completed and blank CRFs, study medication, etc.) must be returned to the sponsor and disposed or archived as directed by the sponsor.

#### Strategies to improve adherence to interventions {11c} and relevant concomitant care permitted or prohibited during the trial {11d}, adverse event reporting and harms {22}

Cross-over between allocated groups because of clinical reasons should be minimized and will be documented. Non-contrast CT scans to assess calcium load if CMR is not sufficient should also be minimized especially by discussing special cases within the TAVR team including TAVR operators and radiologists. Patients included in the study are informed that they should not participate in another experimental study during the study period. Furthermore, no restrictions are made regarding clinical care of the patients. Adverse events will be immediately reported to the sponsor.

### Outcomes {12}

Follow-up will be conducted at discharge as well as 2 years after TAVR. Follow-up study investigations are summarized in Table 1. End-point definitions will be based on the updated 2012 VARC-2 consensus document [37].

**Table 1 Tab1:**
[figure not shown]
Individual study time-table

*TAVR* Transcatheter aortic valve replacement, *CMR* Cardiovascular magnetic resonance, *CT* Computed tomography

#### Primary endpoint

The primary outcome will be a composite clinical efficacy end-point related to implantation success at hospital discharge, based on the VARC-2 criteria [37]Absence of procedural mortalityCorrect positioning of the prosthetic valveIntended performance of the prosthetic valve (mean aortic valve gradient < 20 mmHg and no valve regurgitation > mild)

#### Secondary endpoints

Secondary end-points consist of clinical efficacy and safety end-points at discharge and 2 years.

*Combined safety end-point:*
All-cause mortalityAll strokesLife-threatening bleedingAcute kidney injury—stage 2 or 3 (including renal replacement therapy)Coronary artery obstruction requiring interventionMajor vascular complicationsValve-related dysfunction requiring repeat procedure

*Combined clinical efficacy end-point:*
All-cause mortalityAll strokeHospitalization for aortic valve related symptoms or heart failureNYHA class III or IVProsthetic valve related dysfunction (mean gradient > 20 mmHg or regurgitation > mild)

Furthermore, the two imaging strategies will be compared regarding imaging procedure related variables:Percentage of interpretable scans and scoring of image qualityPercentage of patients with need for an alternative imaging methodDuration of imaging and patient comfortCumulative radiation dose during TAVR planningCumulative amount of contrast agent used for TAVR planningImaging related safety parameters as contrast extravasation, allergic reactions, et cetera.

Finally, biomarker levels at baseline as well as at follow-up visits will be investigated.

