**Methods:**

This is a prospective, randomized, open-label trial. It is planned to include 250 patients with symptomatic severe aortic stenosis scheduled for TAVR based on a local heart-team decision. Patients will be randomized in a 1:1 fashion to receive a predefined TAVR-CMR protocol or to receive a standard TAVR-CT protocol within 2 weeks after inclusion. Follow-up will be performed at hospital discharge after TAVR and after 1 and 2 years. The primary efficacy outcome is device implantation success at discharge. The secondary endpoints are a combined safety endpoint and a combined clinical efficacy endpoint at baseline and at 1 and 2 years, as well as a comparison of imaging procedure related variables. Endpoint definitions are based on the updated 2012 VARC-2 consensus document.

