### Trial design {8}

The present trial is a prospective, randomized, open-label trial to prove the non-inferiority of TAVR-CMR compared to TAVR-CT to guide TAVR. The final analysis will include 226 consecutive patients scheduled for TAVR. According to previous studies, approximately 45% of the patients are female [9]. Therefore, to guarantee gender equity, we aim to enroll at least 80 female patients. Patients will be randomized in a 1:1 fashion to receive a predefined TAVR-CMR protocol or to receive a standard contrast-enhanced TAVR-CT protocol within 2 weeks after inclusion. Inclusion and exclusion criteria are presented below. A detailed study flowchart is presented by Fig. 1. Follow-up for the primary objective will be performed before discharge after TAVR. Extended analysis and clinical follow-up is planned after 2 years.

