## Assignment of interventions: blinding

### Who will be blinded {17a}, procedure for unblinding if needed {17b}

The randomizing physicians are blinded to the allocation table. Due to the nature of the study, the assignment to the study intervention (diagnostic test) and the image interpretation will be performed open-label. Furthermore, TAVR operators are not blinded. Study personnel responsible for the evaluation of end-points will be blinded regarding the allocated intervention. Unblinding procedures are not necessary due to the open-label design of the study.

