## Statistical methods {20a}

Statistical analysis will be performed with SPSS 26.0. (IBM, Armonk, NY, USA) for Windows.

Statistical analysis will be supervised by an independent statistician from the Department of Medical Statistics, Informatics and Health Economics (Innsbruck Medical University). Normally distributed continuous variables will be presented as mean ± standard deviation, not normally distributed continuous variables as median with corresponding interquartile range (IQR). Categorical variables will be displayed as the number and percentage of patients. Pearson or Spearman correlations will be calculated as appropriate. *χ*^2^-test will be used to compare categorical variables between groups. ANOVA with Bonferroni post hoc testing (if ND) and Mann–Whitney-*U* (if not ND) will be used to determine differences in continuous variables between groups. Time-to-event is defined as time from the TAVR procedure to the date of the first end-point. Kaplan–Meier survival curves will be determined and log-rank comparison will be used between groups. Uni- and multivariate Cox-regression analysis will be used to estimate hazard ratios for all left ventricular variables. Factors with univariate association with the primary end-points with significance < 0.1 will be entered in multivariate analysis. For all data a 2-tailed *p*-value of *p* < 0.05 will be considered to indicate statistical significance. No interim analysis is planned.

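### The early secondary composites are read at discharge, a time that varies by patient: the readmission component is empty there and complications soon after discharge fall outside the early comparison

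*Protocol article*

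**What the plan says.** Under Outcomes {12}, the protocol article sets two follow-up times: "Follow-up will be conducted at discharge as well as 2 years after TAVR". The Secondary endpoints section repeats them for both composites: "Secondary end-points consist of clinical efficacy and safety end-points at discharge and 2 years". Each composite has a single component list, with no separate list for discharge. The efficacy list includes hospital admission for valve symptoms or heart failure.

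Other sections give different times. The Methods paragraph of the Abstract says "Follow-up will be performed at hospital discharge after TAVR and after 1 and 2 years", and it places the secondary endpoints as "a combined safety endpoint and a combined clinical efficacy endpoint at baseline and at 1 and 2 years". Trial design {8} says "Extended analysis and clinical follow-up is planned after 2 years" and does not mention 1 year.

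Objectives {7} frames the combined safety endpoint as a non-inferiority question, listed separately from the 2-year extended follow-up. Statistical methods {20a} adds a time-to-event analysis: "Time-to-event is defined as time from the TAVR procedure to the date of the first end-point".

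On the gradient, the Primary endpoint section requires "mean aortic valve gradient < 20 mmHg and no valve regurgitation > mild" for intended valve performance. The secondary efficacy composite counts dysfunction only when the mean gradient is above 20 mmHg.

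**The concern.** Three features of the discharge reading are awkward.

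First, a patient who has not yet left hospital cannot be readmitted. At discharge the efficacy composite therefore carries a component that is zero in both arms by construction, and it does not measure everything it lists.

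Second, discharge is not a fixed time. A patient who leaves early is observed briefly; one kept in because of a complication is observed for longer. Complications soon after leaving fall outside the early safety composite. Because the safety objective is non-inferiority, losing events matters more than it would in a superiority comparison: a smaller observed absolute difference makes non-inferiority easier to declare.

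Third, the same discharge echo with a gradient of exactly 20 mmHg is a failure for the primary endpoint and not a dysfunction for the secondary one.

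At stake is how the early secondary comparison can be interpreted. The primary endpoint is an implantation-success measure at discharge and is not touched.

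**Working it through.** **1. The plan's own figure.** The only sample-size figure is for the primary endpoint (Sample size {14}): 92% success in both groups, margin 9 points, power 80%, 113 per group. With n = (z₁₋α + z₁₋β)² × 2p(1−p) / margin²:

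- one-sided 0.05: (1.645 + 0.842)² × 2 × 0.92 × 0.08 / 0.09² = 112.4, so 113 per group, as stated;
- one-sided 0.025: 143 per group.

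The stated number reproduces at one-sided 0.05. It says nothing about the composites, for which the article gives no event rate, margin or length of stay. Everything in steps 3 to 5 is therefore illustration under labelled assumptions.

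**2. Time points side by side.**

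| Section | Follow-up | Composites read at |
|---|---|---|
| Abstract, Methods | discharge, 1 and 2 years | baseline, 1 and 2 years |
| Trial design {8} | before discharge (primary), 2 years | not stated |
| Outcomes {12} | discharge, 2 years | see next row |
| Secondary endpoints | – | discharge, 2 years |

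These cannot all be right. None gives an early window of fixed length.

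**3. Effect of partial capture on the absolute scale.** Let a share f of early events occur before discharge, equal in both arms. The observed difference is f × (p₂ − p₁), while the risk ratio p₂/p₁ is unchanged. Assume p₁ = 15% and p₂ = 24% over a full early window, n = 113 per arm, and the primary's 9-point margin, borrowed because none is stated for safety. The chance of declaring non-inferiority at one-sided 0.05 is Φ[(0.09 − d)/SE − 1.645], with SE² = [c(1−c) + t(1−t)]/113, c = f·p₁ and t = f·p₂.

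| f | observed d (points) | P(non-inferiority declared) |
|---|---|---|
| 100% | 9.0 | 5% |
| 80% | 7.2 | 10% |
| 60% | 5.4 | 21% |
| 50% | 4.5 | 31% |

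For f = 60%: c = 0.09, t = 0.144, SE = √[(0.0819 + 0.1233)/113] = 0.0426; 0.036/0.0426 − 1.645 = −0.80; Φ(−0.80) = 21%.

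In event counts, with 125 enrolled per arm, an assumed 15% composite rate and 20–40% of events after discharge, 125 × 0.15 × 0.20 to 0.40 = 3.8 to 7.5 events per arm are missed at the early reading.

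**4. Unequal capture.** If both arms truly had 15% but length of stay led to capture of 80% in one and 60% in the other, the early reading would show 12% and 9%: a spurious 3 points, in whichever direction the stay differs.

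**5. The 20 mmHg boundary.** Assume gradients recorded as whole numbers and roughly normal. The column for exactly 20 is P(19.5 < X < 20.5); the column for 20 or more is P(X > 19.5).

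| Assumed mean, SD (mmHg) | exactly 20 | of 250 | 20 or more, of 250 |
|---|---|---|---|
| 9, 4 | 0.2% | 0.6 | about 1 |
| 11, 5 | 1.6% | 4.0 | about 11 |
| 12, 5 | 2.2% | 5.6 | about 17 |

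The plan expects 8% × 250 = 20 primary failures. It builds these from deaths, regurgitation and reinterventions, with nothing allotted to gradient. The two lower rows put 11 to 17 failures on gradient alone and fit that poorly, so the count at exactly 20 is more likely near the low end.

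**The case against.** Several stronger conclusions are tempting, and the documents do not support them.

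- *Readmission is never counted.* Not so. The same list applies at 2 years; the component is empty only at discharge.
- *Post-discharge complications enter only at 2 years.* The Outcomes section reads that way, but the Abstract names 1 year. The time-to-event clock runs from TAVR to the event date and is not tied to a visit, so a dated stroke after discharge can appear at its true time and early separation of the curves would remain visible. This does not define an early composite, but it limits what is lost.
- *The early comparison is biased towards no difference.* This holds only on the absolute scale and only if later events differ in the same direction as in-hospital ones. A proportional loss leaves a risk ratio unchanged, and unequal stay can push either way.
- *Unblinded operators control the window.* The article does say "Furthermore, TAVR operators are not blinded", but the same section blinds those who evaluate endpoints. Nothing states that operators decide discharge or that stay differs by arm. Blinded assessors do not give the window a fixed length, however.

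It is also fair that the visit table is not shown, that the endpoint definitions rest on a consensus document not at hand, and that the article condenses a fuller protocol; an intermediate contact may exist there. Discharge is a defensible reading for in-hospital complications, and a fixed window is partly a design preference. What stands is that the article's text fixes discharge as the early reading, applies to it a component that cannot occur, and disagrees with itself on the schedule and on the gradient boundary.

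**Conclusion.** The point holds in limited form and concerns secondary endpoints only. As written under Outcomes {12}, the early composites include a structurally empty component and a safety window of patient-dependent length, so complications soon after discharge are outside the early comparison though not lost to the trial. The direction of any bias is conditional, and its size cannot be obtained from the documents: the step from 9 to 5.4 points, with the chance of wrongly declaring non-inferiority going from 5% to 21%, rests on assumed rates of 15% and 24%, an assumed 60% capture and a borrowed margin. The gradient mismatch is certain from the text but small, probably affecting a patient or so to a few of 250. The disagreement over time points is also certain and needs settling whatever is decided about the window. A correction is worthwhile because it is cheap and makes the early safety comparison easier to interpret.

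**What to change.** 1. Keep discharge for the primary endpoint.
2. In Outcomes {12} and Secondary endpoints, define the early safety and clinical-efficacy composites over one fixed window from TAVR, for example all events to day 30 whether in or out of hospital. Collect them by one telephone contact or record check. Admission after the index stay then becomes a component that can occur.
3. Reconcile the follow-up and assessment times in the Abstract, Trial design {8}, Outcomes {12} and Secondary endpoints. Say whether there is a 1-year assessment and what a composite at baseline means.
4. Make the gradient limits in the Primary and Secondary endpoints sections complementary, so that exactly 20 mmHg is scored the same way in both.

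The cost is one contact or record check per patient, one CRF page and a protocol amendment. The downside is a little site work. For patients already past the window, early events can be recovered only as far as records allow. Items 3 and 4 are text changes only.

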### Participant timeline {13} and provisions for post-trial care {30}

The time-table for the individual participant is presented in Table 1. After individual completion of the study period, patients are advised to seek regular follow-up examinations at their referring physician. A patient insurance covers cost for compensation of harm.

### Sample size {14} and recruitment {15}

Sample size estimation for the primary endpoint is based on previous data indicating a rate of 4% of early deaths, 4% of valve regurgitation > mild, and 0.4% of reinterventions after TAVR [10]. Therefore, we estimate an implantation success rate of 92% in both study groups. For a non-inferiority margin of 9%, hence 113 patients per group should be included to achieve a statistical power of 80%. A drop-out rate of 10% is assumed. Therefore, it is planned to include a total of 250 patients in the trial.

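### 113 patients per group give 80% power only at a one-sided 5% level; at the two-tailed 0.05 level the protocol sets, power is about 70%

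*Protocol article*

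**What the plan says.** The primary objective is to show that CMR-based planning is non-inferior to CT-based planning for implantation success (Objectives {7}).

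Sample size {14} and recruitment {15} gives the planning assumptions:

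- Success rate: "we estimate an implantation success rate of 92% in both study groups".
- Margin, size and power: "For a non-inferiority margin of 9%, hence 113 patients per group should be included to achieve a statistical power of 80" per cent.
- Attrition and total: "A drop-out rate of 10% is assumed", and "it is planned to include a total of 250 patients in the trial".

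That section gives no alpha and does not say whether the test is one- or two-sided. Trial design {8} specifies 1:1 allocation and repeats the evaluable number: "The final analysis will include 226 consecutive patients scheduled for TAVR", which is 2 × 113.

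The only significance level in the document is in Statistical methods {20a}: "For all data a 2-tailed *p*-value of *p* < 0.05 will be considered to indicate statistical significance". The primary non-inferiority comparison is not exempted. No one-sided level and no 90% confidence interval appears anywhere.

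**The concern.** A non-inferiority claim is one-directional. Testing it at a two-tailed 0.05 level conventionally means requiring the lower limit of the two-sided 95% confidence interval to lie above the negative of the margin, which is a one-sided test at 0.025. The figure of 113 per group looked too small for that level with a 9-point margin and 92% success.

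This affects the trial's one confirmatory claim. If the stated level is applied, the trial has less power than it reports. If the level behind the sample size is applied, the nominal type I error for non-inferiority is double what the statistical section implies. While the two are unreconciled, the document does not say whether the 90% or the 95% interval decides the result, and the verdict can differ between them.

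**Working it through.** **Inputs.** Success 0.92 in each group, so a true difference of 0; margin 0.09; power 80% (all from Sample size {14}); 1:1 allocation and 226 analysed (Trial design {8}); two-tailed 0.05 (Statistical methods {20a}).

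**Formula** (unpooled normal approximation, per group):

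n = (z_α + z_β)² × 2 × p(1 − p) / margin²

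Here 2 × 0.92 × 0.08 = 0.1472, 0.09² = 0.0081, and z_β = 0.8416.

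**Reproducing the protocol's figure, one-sided 0.05** (z_α = 1.6449):

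n = 6.183 × 0.1472 / 0.0081 = 112.4, rounded up to **113**. This matches.

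**At the stated level, one-sided 0.025** (z_α = 1.9600):

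n = 7.849 × 0.1472 / 0.0081 = 142.6, rounded up to **143** per group, or 286 evaluable.

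**Power at the planned size.** Power = Φ(0.09 / √(0.1472 / n) − z_α).

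| n per group | One-sided 0.05 | One-sided 0.025 |
|---|---|---|
| 113 (evaluable target) | 80.2% | 70.3% |
| 125 (all 250 evaluable) | 83.6% | 74.6% |

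For 113 per group the standard error is √(0.1472 / 113) = 0.0361 and 0.09 / 0.0361 = 2.494. Then Φ(2.494 − 1.960) = 0.703 and Φ(2.494 − 1.645) = 0.802.

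**Exact check.** Enumerating all binomial outcomes for 113 per group with the Wald interval gives power of 79.8% at one-sided 0.05 and 70.8% at one-sided 0.025.

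**Could another method give 113 at the stated level?** None of those tried does:

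| Method | n at one-sided 0.05 | n at one-sided 0.025 |
|---|---|---|
| Unpooled normal approximation | 113 | 143 |
| With continuity correction | 134 | 165 |
| Farrington–Manning | 126 | 161 |

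An equivalence design (two one-sided tests at 0.05) needs 156. A test of difference between 92% and 83% needs 166 (one-sided 0.05) or 211 (two-sided 0.05).

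**Where the two levels disagree.** With the planning standard error of 0.0361, the 95% interval excludes the margin if the observed difference is above −0.09 + 1.960 × 0.0361 = −0.019. The 90% interval does so above −0.09 + 1.645 × 0.0361 = −0.031. An observed deficit of roughly 1.9 to 3.1 percentage points would pass one rule and fail the other. If the groups are truly equal, the chance of landing there is about 80.2% − 70.3% = 9.9%.

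**The case against.** The strongest reply is that 113 is not a miscalculation. It follows exactly from a recognised non-inferiority convention, one-sided 5%. The article condenses a longer protocol that may state that level. The statistical methods section lists chi-square, ANOVA, Mann–Whitney, log-rank and Cox methods and describes no non-inferiority test, so its two-tailed threshold could be read as the rule for tests of difference only. Converting two-tailed 0.05 into one-sided 0.025 is a convention and is not spelled out in the document.

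Part of this stands. The fault is an inconsistency between two sections, not a slip in the formula. The one-sided 5% level is inferred by back-calculation, because no sample-size method is named. A one-sided 5% test can be defended if it is declared and justified. An unseen analysis plan might also already fix which interval decides.

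The narrow reading of the threshold does not stand. The sentence is unqualified in scope, the primary objective is non-inferiority, and no other level is given. If an unseen document does specify one-sided 5%, the sentence here is wrong for the primary test and still has to be changed.

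The power figure also depends on the method: Farrington–Manning gives 64.2% at one-sided 0.025 with 113 per group, so 70% is not the most pessimistic value. A smaller point is that the three event rates quoted in the sample-size section sum to 4% + 4% + 0.4% = 8.4%. That implies 91.6% success and 68.4% power at one-sided 0.025. It assumes that the events do not overlap and that reinterventions count as failures, and the conclusion does not rest on it.

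**Conclusion.** The concern holds. At the only significance level the document states, 113 per group give about 70% power (70.3% by normal approximation, 70.8% by exact enumeration of the Wald interval), not 80%. Reaching 80% at that level needs 143 evaluable per group. The dropout allowance does not close the gap: with all 250 evaluable, power is 74.6%. The 80% figure is right only at one-sided 5%, which the document never states and which its general rule contradicts.

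This rests on the protocol's own 92% and 9-point figures, no true difference between groups, and the usual correspondence between a two-tailed 0.05 level and a one-sided 0.025 non-inferiority test. It must be corrected, because it concerns the error rates of the primary claim.

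**What to change.** State the significance level and its sidedness in Sample size {14}, and use the same level for the primary test in Statistical methods {20a}. Do this before the data are analysed. Two routes need only wording:

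1. **Preferred:** keep the two-sided 95% confidence interval (one-sided 2.5%) for the primary non-inferiority test. Restate power as about 70% for 113 per group, naming the method.
2. **Alternative:** declare that the primary test is one-sided at 5% (two-sided 90% interval), justify that choice, and exempt the test from the general two-tailed 0.05 rule. The 80% power statement then stands.

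Neither route needs more patients. The first makes the reported power less favourable; the second openly accepts a 5% nominal risk of a false non-inferiority claim. Keeping both 80% power and the two-sided 95% interval would need 143 evaluable per group, or 286 / 0.9 = 318 randomised after rounding up, against the planned 250.
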